# **Metformin treatment of pregnant PCOS women and prevention of preterm birth**

## **The PregMet 2 Study**

EudraCT number 2011-002203-15

Version 7

A prospective, randomized, double-blind, multi-centre study, where the possible effect of metformin to prevent late miscarriage and preterm delivery is studied in women with polycystic ovary syndrome (PCOS).

## **Summary**

### *Background*

PCOS is a common condition among women of fertile age. It can affect almost all aspects of life and reproductive health. The prevalence of pregnancy complications, such as gestational diabetes, preeclampsia, miscarriage and preterm birth seems to be increased among PCOS women. The prevalence of PCOS among women who have experienced preterm delivery is also increased (30 %), compared to a normal population (31). Data from the control women from the same study indicate a 15% prevalence of PCOS in Norwegian women of fertile age. Pooled data from our former RCTs indicates that metformin treatment in pregnancy might prevent late miscarriages and preterm births (1, 2).

### *Aim*

The main aim of the PregMet 2 Study is to investigate whether metformin prevents late miscarriages and preterm deliveries in PCOS women treated with metformin from first trimester of pregnancy to delivery in a large randomized, controlled, multi-centre trial setting.

### *Material and methods*

We will include 18-45 year old women, with PCOS diagnosed according to Rotterdam criteria and with singleton pregnancies, in the first trimester of pregnancy. The participants will be randomized double blindly to 1000 mg metformin twice daily or placebo, from inclusion to delivery. Five prescheduled visits are planned, where we intend to measure weight, blood pressure, perform ultrasound examinations and draw blood samples and perform oral glucose tolerance tests (OGTT).

## **Introduction**

### *PCOS*

The polycystic ovary syndrome (PCOS) affects some 8 -11% of women in the reproductive age group diagnosed according to National Institute of Health criteria (NIH) (3-5) and probably up to 15-20 % according to The Rotterdam Consensus criteria.

The cornerstones of PCOS are insulin resistance and hyperandrogenicity, although none is mandatory for the diagnosis according to the Rotterdam criteria (6). PCOS has implications both for fertility and pregnancy outcome, while an increasing body of evidence points to a high prevalence of pregnancy complications (7-11). Hyperinsulinemia and hyperandrogenism have been suggested as pathogenic factors in both PCOS and pregnancy complications (12-14) .

### *Preterm birth*

Data on women who had experienced preterm delivery in the county of Namdalen (Namsos hospital) shows a PCOS prevalence of 30 % (ref). The PCOS prevalence among controls who had given birth at term after an uncomplicated pregnancy was 15%.

### *Metformin*

Metformin, an insulin-sensitizer used in the treatment of type 2 diabetes, reduces fasting insulin and testosterone levels in non-obese, non-pregnant PCOS women (15). During the last decade, several retrospective and non-randomized studies have reported beneficial effects of metformin on pregnancy loss and pregnancy complications, in particular gestational diabetes mellitus (GDM) (7, 11, 16-21).

### *The Pilot study*

Our research group performed a pilot study on metformin treatment of pregnant PCOS women in 2000 - 2003. In this pilot study 7 out of 22 placebo-treated PCOS women experienced serious pregnancy complications, while none of the 18 metformin-treated women had such complications. These were promising results.

### *The PregMet 1 Study*

To confirm these results, a Norwegian multicentre trial, the PregMet 1 Study, was conducted by [name] as the principal investigator. However, metformin treatment from the first trimester to delivery, did not influence the incidence of gestational diabetes mellitus (GDM),

preeclampsia (PE), preterm birth (gestational week 22-37), or the composite of these three end points when analysing the results according to *“intention to treat principal”* (2).

**Table 1. The PregMet 1 Study: Primary endpoint results**

|                           | Metformin
N = 135 | Placebo
N = 135   | 95% CI              | Pvalue      |
|---------------------------|----------------------|----------------------|---------------------|-------------|
| Preeclampsia              | 10/135 (7.4)         | 5/135 (3.7)          | -1.7 to 9.2         | 0.18        |
| Preterm delivery          | 5/135 (3.7)          | 11/135 (8.2)         | -10.1 to 1.2        | 0.12        |
| New GDM                   | 22/125 (17.6)        | 21/124 (16.9)        | -8.6 to 10.2        | 0.87        |
| Composite endpoint | 35/135 (25.9) | 33/135 (24.4) | -8.9 to 11.3 | 0.78 |

An editorial in Journal of Clinical Endocrinology and Metabolism accompanying the publication of the PregMet 1 Study stated that:

*“There is no study of metformin during pregnancy in women with PCOS that even comes close to this one in terms of scope and quality. This is today the alpha and the omega of metformin use in pregnancy in women with PCOS, the best level I evidence we have to counsel our patients....”(22)*

### *Preterm birth*

The WHO defines preterm labour as labour occurring before 37 weeks of pregnancy or before 259 days of pregnancy (A). As prognosis depends on gestational age at birth, we further subdivide preterm deliveries into following groups (23):

- Late preterm birth                      34 - 36+6 weeks
- Moderately preterm birth            32 - 33+6 weeks
- Very preterm birth                      28 - 32+6 weeks
- Extremely preterm birth              < 28 weeks

About 10% of preterm deliveries are extremely preterm, another 10 % very preterm and approximately 80 % moderately or late preterm deliveries.

The obstetric precursors leading to preterm birth are:

1. Delivery for maternal or fetal indications, in which labor is either induced or the infant is delivered by prelabor caesarean section;
2. Spontaneous preterm labor with intact membranes; and
3. Preterm premature rupture of the membranes (PPROM), irrespective of whether delivery is vaginal or by caesarean section (24).

Figure 1 (25, 26).

[figure not shown]

Preterm delivery is a major contributor to neonatal morbidity and mortality (27).

Epidemiological risk factors such as socioeconomic status and ethnicity seems to be important (26). Infections, uterine distension and anomaly are other known factors related to

preterm birth. However, the causes of preterm delivery are still essentially unknown and seem to be multifactorial (25).

Former preterm delivery is a significant risk factor. However, almost 50 % of preterm births occur without any identified cause or risk factor (25). The incidence of preterm birth is rising in most western countries, Norway included (28). This occurs despite all attempts to treat and prevent preterm birth.

The fact that former preterm labour is a strong risk factor, indicate a genetic or otherwise individual disposition. And the more or less universal rise in preterm birth rates in the Western world indicates that environmental or lifestyle risk factor changes are involved

Incidence of preterm labour:

Incidence in Norway (B) : 1980: 5.6 %

1995: 7.5 %

1999: 7.9 %

Incidence in the USA (C): 1980: 8 %

1995: 12 %

Although most preterm babies survive, they are at increased risk of neuro-developmental impairments, respiratory and gastrointestinal complications. Preterm infants are also of increased risk of developing cognitive and behavioral abnormalities and of achieving poorly in educational situations. These problems tend to last until adulthood (29). Recent evidence also indicate that infants born close to term (gestational week 34-36) carry a risk of increased morbidity and mortality risk, compared with term infants(E).

There are major socioeconomic costs connected to these patients. There are obvious costs due to initial neonatal treatment. But even more substantial is the health service costs following

discharge from the neonatal unit. This also represents long-term burdens, on affected families, but also on health, education and social services (30).

Recently published data on women who had at least one preterm birth, showed a PCOS prevalence of 25%, while 14% had PCOS among a control group of women who had given birth at term after an uncomplicated pregnancy (31). These data support former reports on preterm deliveries occurring more often among PCOS women and points to the fact that there is an increased prevalence of PCOS among women who experienced preterm birth.

### *Pooled data and per protocol analyses*

In the PregMet 1 Study we found that, according to “*intention to treat*” analysis, 5 out of 135 metformin-treated and 11 out of 135 placebo-treated PCOS women experienced preterm birth ( $p=0.12$ ).

However,

- Biologically and medically, late miscarriage (gestational week 13-21) and preterm birth is a “continuum”, not separate conditions. Adding the miscarriage and preterm data in the PregMet 1 Study and analyzing it according to “*intention to treat*” principle, we find 13 late miscarriages/preterm births in the placebo group ( $N=135$ ) and 5 in the metformin group ( $N=135$ ), ( $p=0.055$ ).

Protocol for The PregMet 2 Study; version 7  
2013-11-25

- If we pool the results from the Pilot Study and the PregMet 1 study, we have 18 of 157 (11.5%) late miscarriages/preterm births in the placebo group and 5 of 153 (3.3%) in the metformin group ( $p=0.01$ ).
- In "*per protocol*" analysis including only women with good drug compliance (drugs taken as intended or 1-2 tablets for a maximum of 4 weeks or no tablets for a maximum of 2 weeks; 84%) of the PregMet 1 Study, 3 out of 108 (2.8%) metformin-treated and 11 out of 108 (10.2%) placebo-treated women delivered preterm,  $p = 0.04$ .
- Adding the miscarriage and preterm data from the Pilot study to the PregMet 1 Study, and analyzing it "*per protocol*" we find that 18 of 129 (14.0%) women in the placebo group and 3 out of 125 (2.4%) in the metformin group had either late miscarriage or preterm birth, i.e.  $< 37$  gestational week ( $p = 0.001$ ). This yields a number needed to treat (NNT) = 8.7 to prevent one late miscarriage or preterm birth.

**Table 2. Per protocol analyses of the Pilot and PregMet 1 studies**

| Placebo                                             |                        | Metformin N = 129    N = 125 |                        |
|-----------------------------------------------------|------------------------|------------------------------|------------------------|
| Gestational age in weeks at miscarriage or delivery |                        |                              |                        |
| Pilot study                                  | PregMet 1 Study | Pilot study           | PregMet 1 Study |
| 21                                                  | 17                     | None                         | 35                     |
| 29                                                  | 21                     |                              | 36                     |
| 31                                                  | 30                     |                              | 36                     |
| 36                                                  | 31                     |                              |                        |
| 36                                                  | 32                     |                              |                        |
|                                                     | 32                     |                              |                        |
|                                                     | 34                     |                              |                        |
|                                                     | 34                     |                              |                        |
|                                                     | 34                     |                              |                        |
|                                                     | 34                     |                              |                        |
|                                                     | 36                     |                              |                        |
|                                                     | 36                     |                              |                        |
|                                                     | 36                     |                              |                        |

### *Costs in suffering*

Both short and long-term costs in money and sufferings of preterm birth are immense.

Although preterm babies born at week 35-37 can be a medical challenge, the real suffering for the patients and relatives, and the costs for the society are often the babies born < gestational week 35. In the present material, 12 out of 18 preterm deliveries and late miscarriages in the

Protocol for The PregMet 2 Study; version 7  
2013-11-25

placebo group, were born < gestational week 35. None were born < 35 gestational weeks among metformin treated women taking their medication as prescribed.

*The treatment costs (from delivery to discharge) for a preterm baby in average are (F)*  
< 1000 g (< 27 weeks) 770 000 NOK

1000g – 1500g (around 27-30 weeks) 575 000 NOK

1500g – 2500g (around 30 – 35 weeks) 240 000 NOK (36)

None of the preterm babies in the metformin-group had birth weight < 2500g, while 9 babies in the placebo group had a birth weight between 1500g – 2500g. The initial treatment cost for these neonates was around 2.2 million NOK. Later costs for treatment of associated conditions and diseases, pedagogic support etc. adds to these initial costs. For example, tuition costs/pedagogic support for a multi-handicapped pupil at grade 11, is 700000 NOK/year and for a handicapped pupil with individual learning goals is 400000 NOK/year (South Trøndelag county 2010)

*Cost versus benefit with metformin treatment*

To treat one pregnant PCOS woman with metformin 1000 mg x 2 daily from gestational week 8 to 37 costs 100 Euro. To prevent one preterm birth or late miscarriage would cost 870 Euro, about 7000 NOK. If we have conservative estimates of the effect used in the power calculation, we find that 20 women have to be treated to prevent one preterm birth. That would be 2 000 Euro or 16 000 NOK. This equals 6-7% of the immediate costs of one preterm baby.

Accordingly, the above described treatment would, if it can be verified in the PregMet 2 Study, probably be among the most cost effective, preventive treatments ever. Actually, metformin is so cheap, old and safe that the pharmaceutical industry does not support research on its effects. This matter has been addressed and discussed at international meetings and congresses and is regarded as a problem.

These results from the PregMet 1 Study and the sub analyses presented above on preterm birth were presented at the NFOG (Nordic Federation of Societies of Obstetrics and Gynecology) PCOS meeting in Copenhagen in November 2010. There was a great interest and enthusiasm for the possible effect of metformin on preterm birth and a call for an international multicentre study to settle this important clinical question as soon as possible.

### **Aim of the PregMet 2 study**

The overall aim and primary end point of the PregMet 2 Study is to investigate whether metformin prevents late miscarriages and preterm deliveries in PCOS women treated with metformin from first trimester of pregnancy to delivery in a large, randomized, controlled, multi-centre trial setting.

### **Hypothesis**

Metformin compared to placebo treatment from the first trimester to term, reduces the prevalence of late miscarriage (gestational week 13-22) and preterm birth (gestational week < 37) in PCOS women diagnosed according to Rotterdam 2003 consensus criteria, with singleton pregnancy.

### **Definitions**

#### *Oligo-amenorrhea*

Defined as a cycle length of  $\geq 35$  days or  $< 10$  per year.

#### *Hyperandrogenism*

- Biochemical hyperandrogenemia:  
(s-testosterone  $\geq$  reference value for women at each study site for the time being and/or s- SHBG  $\leq 30$  nmol/L).

- Clinical hirsutism: Ferriman-Gallwey score  $> 6$

*Polycystic ovaries by ultrasound*

Defined as at least 12 follicles in one ovary and/or an ovarian volume  $\geq 10$  ml (volume =  $0.52 \cdot d^1 \cdot d^2 \cdot d^3$ ) in at least one ovary.

If there is a follicle  $\geq 10$  mm, repeat ultrasound at the time of ovarian quiescence

*Polycystic ovary (PCO)*

□ 12 or more follicles in the ovary, each follicle measuring 2-9 mm in diameter and/or

*PCOS: at least 2 out of 3 criteria*

1. PCO in at least one ovary
2. Oligo-/anovulation (clinically diagnosed as oligo-/amenorrhea, i.e. menstrual cycles  $> 35$  days or  $< 10$  menstruations/year
3. Hyperandrogenism; clinical or biochemical: Biochemical hyperandrogenemia (testosterone above upper reference value at the actual laboratory used) and/or clinical hirsutism (defined in this study as weekly Ferriman-Gallwey score  $\geq 6$ )

Exclusion of: Congenital adrenal hyperplasia (CAH), non-classical CAH, Cushing disease, acromegaly and androgen secreting tumors.

*Gestational age:*

Protocol for The PregMet 2 Study; version 7  
2013-11-25

Gestational age is determined in the first trimester by a vaginal ultrasound examination.

Crown-rump-length (CRL) and/or bi-parietal diameter (BPD) are measured.

*Term date:*

Term date is determined by a mid-second trimester, trans-abdominal ultrasound examination measuring BPD, mean abdominal diameter (MAD) and length of femur, or using the appropriate method that is standard at the actual study site.

*Late miscarriage:*

Miscarriage occurring between gestational weeks 13 + 0 and 22 + 6.

*Preterm birth:*

Spontaneous or operative birth occurring before gestational week 37 + 0.

*Hypertension in pregnancy:*

Blood pressure measured after at least 10 minutes of comfortable chair rest  $\geq 140/90$  mmHg at two different occasions without proteinuria or other signs of preeclampsia occurring after week 20 in pregnancy.

*Preeclampsia:*

Blood pressure measured after at least 10 minutes of comfortable chair rest  $\geq 140/90$  mm Hg at two different occasions and proteinuria (1+ protein in two different occasions or 2+ protein in one occasion on a urinary dip stick).

### *Gestational diabetes mellitus:*

Gestational diabetes mellitus (GDM) is defined as a fasting plasma glucose  $\geq 7.0$  mmol/L or a 2 hour plasma glucose  $\geq 7.8$  mmol/L during a standard 75 g per oral glucose tolerance test (OGTT) performed according to the WHO standard.

### *Hirsutism:*

Ferriman – Gallwey score  $\geq 6$

## **The endpoints of the study**

### *Primary endpoint*

- The combined incidence of late miscarriages and preterm births. This includes spontaneous births, induced vaginal deliveries and operative deliveries on medical indications.

*Secondary endpoints*

- No. of patients treated with vaginal progesterone indicated by short cervix as a sign of imminent preterm delivery
- NICU admissions and total number of days in NICU/baby
- No. of patients hospitalized (except delivery and post partum)
- Total number of hospitalization days/ hospitalized participant
- The incidence of gestational diabetes mellitus
- The prevalence of :
  - Preeclampsia ○
  - Hypertension in pregnancy
- Vaginal bleeding in pregnancy

*Tertiary endpoints*

- Safety of treatment with metformin
- Weight gain in pregnancy
- Newborn data
- Birth weight
- Birth length
- Head circumference
- Apgar score/
- pH and base excess(BE) from umbilical cord blood

- Malformations

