### *Inclusion criteria*

- Age: 18-45 years
- PCOS diagnosed according to Rotterdam 2003 criteria,
- Mode of conception: Any
- Single, viable fetus, diagnosed by vaginal ultrasound
- Gestational week at inclusion: week 6 + 0 to 12 + 6.
- Wash out for metformin: at least 7 days
- Able to communicate fluently in the official language at the study site or English

- Informed consent

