## Clarification:

«**Drop-out**»: is a general term for those patients included in a study who

- Clearly state that they do not want to continue in the study, (-they will not meet at pre-scheduled visits in the study) OR
- Clearly state that they do not intend to take any more study medication OR
- Clearly state that they do not want any contact with the study investigators

**NOT “Drop-out”**: patients who

- Miss/forget an appointment, but attend other visits
- Reduce or do not take study medication because of side effects □ Forget to take their study medication, but intend to take it.

**In our “intention-to-treat analyses” we will include data from all “drop-outs”. This is the meaning of “intention-to-treat”.**

Data included from drop-outs are:

- already collected data and samples and
- Information from delivery mother/baby. (The informed consent has not been withdrawn)
- **Already collected data will not be destroyed or deleted routinely**, but if the patient explicitly asks for it (withdraws informed consent); we will delete it and not collect information from her delivery and baby at delivery.

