## **Adverse events**

### *Definition*

#### *Adverse event (AE)*

An adverse event (AE) is defined as any untoward medical occurrence in a patient or clinical investigation subject administered a pharmaceutical product, which does not necessarily have a causal relationship with this treatment. An AE can therefore be any unfavourable and

unintended sign (including an abnormal laboratory finding), symptom, or disease temporarily associated with the use of a medical product, whether or not related to the medical product.

*Serious adverse events (SAE)*

Any serious adverse events (SAE) arising during the study must be reported to the principal investigator of the study within 24 hours. SAE is defined as any untoward medical occurrence that at any dose:

- Results in death,
- Is life-threatening (i.e. the patient was at risk of death at the time of the event. It does not refer to an event, which hypothetically might have caused death if it was more severe).
- Requires in-patient hospitalisation or prolongation of existing hospitalisation.

*SAE not to be reported;*

Conditions to be reported as study endpoints, **and not as SAE**, even if they are leading to hospitalization.

- Gestational diabetes
- Preeclampsia and severe hypertonia
- Preterm delivery
- Miscarriage
- Preterm rupture of membranes
- Severe intrauterine growth restriction

Protocol for The PregMet 2 Study; version 7  
2013-11-25

- Severe bleeding in pregnancy

*In the case of an SAE please refer to:* Principal investigator, Dr.med [name], St.Olavs Hospital, Trondheim,

Phone office: [contact]

Mobile phone [name]

Study [contact]

E-mail: [[contact]](mailto:[contact])

**SUSAR** (Suspected Unexpected Serious Adverse Reactions)

According to “Regulation relating to clinical trials on medicinal products for human use”, the sponsor shall ensure that all suspected adverse reactions occurring in connection with a clinical trial of drugs for human beings that are fatal or life-threatening, and which are unexpected, are reported. The same is applicable for suspected adverse reactions that are serious and unexpected

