### **Statistical analyses**

Statistical analysis of the data will be performed when all data are collected and quality checked. Data will be analyzed by an experienced statistician at Unit for Applied Clinical Research according to the “pentablind” approach.

The main outcome (late abortions and preterm births) will be the end points by intention to treat (ITT) analyses. However, secondary “per protocol” analysis will also be performed. The metformin group will be compared to the placebo group using non-paired parametric and non-paired non-parametric methods as appropriate. Only two-sided tests will be used.

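### Pregnancy loss between randomisation and 12+6 is in no named endpoint, yet it is exempt from SAE reporting as if it were one

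*Protocol*

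**What the plan says.** - **Entry and treatment.** Inclusion criteria: "Gestational week at inclusion: week 6 + 0 to 12 + 6". Summary, Material and methods: "The participants will be randomized double blindly to 1000 mg metformin twice daily or placebo, from inclusion to delivery".
- **Endpoint.** The primary endpoint is "The combined incidence of late miscarriages and preterm births". Under Definitions, late miscarriage is "Miscarriage occurring between gestational weeks 13 + 0 and 22 + 6" and preterm birth is "Spontaneous or operative birth occurring before gestational week 37 + 0". The Hypothesis section also starts at week 13.
- **Analysis set.** Statistical analyses: "The main outcome (late abortions and preterm births) will be the end points by intention to treat (ITT) analyses". The section on drop-outs keeps women who stop medication or miss visits, and its clarification says "we will include data from all" drop-outs. It defines these as women who decline visits, drug or contact. It does not mention women whose pregnancy has ended.
- **Other endpoints.** No secondary or tertiary endpoint names miscarriage before 13+0. The nearest items are vaginal bleeding, hospitalisation and a general entry for metformin safety.
- **Safety reporting.** Under Adverse events, the list of SAEs not to be reported is introduced by "Conditions to be reported as study endpoints". One entry is miscarriage, with no gestational limit.

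**The concern.** Study drug can start up to 7 weeks before the endpoint window opens (6+0 to 13+0). A loss in that interval makes the primary event impossible. It is a competing event that occurs on treatment and lies outside the composite.

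If metformin changes early loss, the primary result cannot show it. An excess on metformin would sit among the non-events. A reduction would leave more metformin pregnancies at risk after week 13 and count slightly against the drug. The protocol gives reason to expect that early loss may respond to treatment: its introduction cites non-randomised studies of metformin and pregnancy loss, and two titles in its reference list concern first-trimester or early loss.

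Safety reporting would normally catch such an effect. Here early loss is removed from SAE reporting on the ground that it is an endpoint, and the endpoint list does not contain it.

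**Working it through.** **Reproducing the plan's figure.** Inputs from Power calculation and Risk of type I errors: 10% v 5%, two-sided alpha 0.05, power 85%, 500 per arm. With pooled variance and no continuity correction:

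n = [1.960 × √(2 × 0.075 × 0.925) + 1.036 × √(0.10 × 0.90 + 0.05 × 0.95)]² / 0.05² = (0.730 + 0.384)² / 0.0025 ≈ 497 per arm.

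Power at 500 per arm is 85.2%. The stated figure reproduces, and no early-loss rate enters it.

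**Notation.** The protocol gives no rate of loss between randomisation and 12+6, so every value of e below is an assumption. Let e be that rate in an arm, and take 10% (placebo) and 5% (metformin) as the event rates among pregnancies reaching 13+0.

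- Primary rate in all randomised women: p × (1 − e)
- Any loss or birth before 37+0: e + p × (1 − e)

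**Equal loss in both arms: effect on power, 500 per arm**

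| e | Primary rates | Power, primary | Any loss or preterm birth | Power, all-loss composite |
|---|---|---|---|---|
| 2% | 9.8% v 4.9% | 84.5% | 11.8% v 6.9% | 75.9% |
| 3% | 9.7% v 4.85% | 84.1% | 12.7% v 7.85% | 71.5% |
| 8% | 9.2% v 4.6% | 81.9% | 17.2% v 12.6% | 53.3% |
| 10% | 9.0% v 4.5% | 81.0% | 19.0% v 14.5% | 47.8% |

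The last column assumes that the drug has no effect on early loss. Equal loss of up to 10% costs the primary analysis about 4 points of power.

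**Unequal loss: bias in the primary risk ratio.** Take 3% on placebo and 5% on metformin, a 2-point excess.

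- Planned halving: (0.05 × 0.95) / (0.10 × 0.97) = 4.75% / 9.7% = 0.49, against 0.50.
- No late effect: 9.5% / 9.7% = 0.98, against 1.00.

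The excess is 0.02 × 500 = 10 women. They remove only the primary events they would have had: 10 × 5% = 0.5, or 10 × 10% = 1.0. With 3% v 8%, a null ratio moves to 9.2% / 9.7% = 0.95.

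**Unequal loss: net result with late events halved**

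| Early loss, placebo v metformin | Primary | Any loss or preterm birth | Net difference |
|---|---|---|---|
| 3% v 3% | 9.7% v 4.85% | 12.7% v 7.85% | 4.85 points |
| 3% v 5% | 9.7% v 4.75% | 12.7% v 9.75% | 2.95 points |
| 3% v 8% | 9.7% v 4.6% | 12.7% v 12.6% | 0.1 points |

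The primary contrast barely changes down the table, while the net benefit falls to almost nothing. Break-even against 12.7% requires 0.05 + 0.95e = 0.127, so e = 8.1% on metformin. That is 5.1 points above placebo, or about 26 women of 500.

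**The case against.** **The week-13 start is deliberate.** The section on pooled data and the section on type I errors treat late miscarriage and preterm birth as a continuum, and the hypothesis claims no more than that. This stands, and the primary endpoint need not change.

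**Scoring as a non-event is not written down.** A reader might infer that the protocol scores an early loss as a success. That is a deduction from the definitions, intention to treat and the absence of an exclusion. The analysis plan, which is not at hand, could classify these women otherwise. Removing them, however, would be a post-randomisation exclusion that the drop-out section does not provide for. The conflict between the endpoint list and the SAE exemption is protocol text, and an analysis plan does not resolve it by itself.

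**Early loss may surface elsewhere.** A reader might infer that the trial could never compare it by arm. That is too strong. The metformin safety item, vaginal bleeding or hospitalisation counts may catch some losses, and the list of minor conditions not reported as adverse events does not include miscarriage. None of these isolates early loss.

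**The bias is slight.** One might set ten extra early losses against the 25 events the trial plans to prevent (50 v 25) and conclude that the primary result is distorted by 40%. It is not: the ratio moves by about 2%. The comparison of 10 with 25 concerns net benefit under an assumed harm. Nothing in the document suggests that metformin raises early loss; one cited title points the other way.

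**Power is not at issue.** The dilution above presumes that 10% is the rate from week 13 onwards. If it is already an all-randomised rate, as the intention-to-treat label on the first trial's 13/135 (9.6%) would suggest, there is no dilution.

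**Conclusion.** The point holds as a gap in endpoint and safety capture. Loss between randomisation and 12+6 occurs on study drug and cannot count in the primary composite. It is named at no endpoint level, and it is exempted from SAE reporting on a ground that the endpoint list does not support.

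The primary risk ratio is only trivially affected (about 2% for a 2-point imbalance), and 500 per arm is sound. What the plan lacks is a means to show that a positive primary result is not offset by early losses. A full offset needs an imbalance of about 5 points (3% v 8%); a 2-point imbalance would reduce the net difference from 4.85 to 2.95 points. These sizes rest on assumed early-loss rates and on the planned halving of late events. They show what could go unseen and do not predict harm. This should be fixed before analysis, but it does not undermine the design.

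**What to change.** Keep the primary endpoint and the sample size, and make three changes.

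1. List miscarriage from randomisation to 12+6 as a secondary or safety endpoint, compared by arm in all randomised women. State that such a loss is a non-event in the primary analysis, if that is the intention.
2. Add one supportive intention-to-treat analysis of any pregnancy loss or birth from randomisation to before 37+0. Present it as descriptive, with an estimate and confidence interval. Its power at 500 per arm is about 72% to 48% for assumed early loss of 3% to 10%, so it should not be a condition for the primary claim.
3. Reconcile the SAE exemption with the endpoint list, so that every early loss is captured either as a named endpoint or as a safety event.

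The cost is a few lines of text and one or two more reported results. The date of each loss is needed. Classifying a miscarriage as late already requires it, but the case report form should be checked to confirm that it is recorded for losses before 13+0.
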